### Measures

#### Asthma Measures

Asthma control will be measured using the validated ACQ [25]. Asthma quality of life will be measured using the mini-asthma quality of life measure, a well-validated survey [26]. Asthma exacerbation will be defined as the need for systemic corticosteroids, hospital admission, or emergency treatment for worsening asthma. This will be self-reported, and the time frame will be captured at 3- and 6-month time frames (Table S2 in Multimedia Appendix 2). Health care use is defined as the number of urgent care or emergency room or hospitalization visits. This will be self-reported, and the time frame will be in 3- and 6-month time frames (Table S2 in Multimedia Appendix 2). Spirometry will be performed using standard procedures at baseline, 24, and 48 weeks. Asthma severity will be assessed per the National Heart Lung and Blood Institute National Guidelines for Asthma management based on current asthma treatment [27].

#### PA Measures

Given that the intervention centers on increasing PA levels through walking, it is important to accurately assess the changes in health-enhancing PA among intervention and control participants throughout the study period. Health-enhancing PA is defined as having MVPA and can occur in the domains of discretionary time, travel, home, or work [17]. Our intervention focuses on increasing overall MVPA levels by adding time spent in moderate-intensity PA during discretionary time, through walking. We will measure domain-specific PA through self-reported data for the full sample. We will also measure PA objectively in half of the sample, as this is a more cost-prohibitive assessment instrument.

#### Accelerometry

MVPA (minutes per day) at baseline (before randomization), 12, 24, and 48 weeks will be assessed objectively using accelerometry. During each assessment period, accelerometer data will be collected over 7 consecutive days using the ActiGraph wGT3X-BT activity monitor (ActiGraph, LLC), a small, triaxial piezoelectric accelerometer (4.6 cm×3.3 cm×1.5 cm; 19 g) that will be worn around the waist on an elastic belt. Accelerometry data will be collected using a standardized protocol. ActiGraph monitors have been extensively validated in laboratory and free-living conditions [28]. At the first data collection appointment, study staff will introduce the accelerometer and provide participants with verbal instructions and a package that includes (1) an initialized accelerometer, (2) detailed written wear instructions, (3) tracking log, (4) contact information, and (5) a padded prepaid trackable envelope to return the devices after concluding the 7-day wear period.

In the tracking log, participants will enter the (1) time they put the monitor on in the morning, (2) time removed it in the evening, and (3) time that the monitor was removed and replaced for ≥30 minutes throughout the day (eg, bathing or swimming activities). Raw triaxial data will be sampled at 40 Hz for 7 consecutive days. Once the accelerometer and tracking log are returned by the participant, data will be downloaded by the study staff and prepared for processing and analysis. Data will be processed using ActiLife software (ActiGraph) through a digitally matched filter, reintegrated up to a 60-s epoch, and screened for wear time using the Choi algorithm [29]. Weekly summary accelerometer estimates will be averaged (across days) for all participants with ≥4 valid days of ≥10 hours per day of wear time (minimum wear time to consider the data valid for analysis). If insufficient wear time is detected, the participant will be contacted and asked to rewear the device to provide valid data. Average accelerometer counts (per minute per day) will be calculated using summed daily counts detected over wear periods, and vector magnitude will be calculated as the square root of the sum of the squares obtained from each axis (ie, 3) of data. Time (ie, minutes per day) spent sedentary and in light-, moderate-, and vigorous-intensity physical will be estimated using Freedson cut points (for adults) based on triaxial data [30]. Data checks, including a descriptive analysis of the accelerometer estimates, will be performed quarterly.

#### Self-Reported Discretionary Time and Travel-Based PA

Self-report data adds rich context that accelerometers lack [31]. Our self-report measures will provide information on the domain (eg, recreational and transportation) of PA. These data will be important to quantify the effect of the intervention in increasing leisure-time walking (its main intention), as well as any potential unintended consequence in increasing or decreasing time spent on other types of activities. Participants will self-report PA using the Past Week Modifiable Activity Questionnaire (PWMAQ). The Modifiable Activity Questionnaire is a self-report instrument that assesses leisure PAs over the past 7 days [32,33]. The structure of the PWMAQ is similar to the Modifiable Activity Questionnaire and includes questions that quantify occupational activity (eg, sedentary, low, and high active occupations), active transport, and common sedentary behaviors. The PWMAQ includes information on 38 leisure-time PAs common among diverse adults. The PWMAQ has been shown to be a reliable and valid measure of PA compared to accelerometry and physical fitness [34,35].

#### Additional PA-Related Measures

Self-efficacy for walking, social support for exercise, and self-regulation will also be assessed as they constitute behavioral mediators for attaining increased PA levels, and the physiologic response to increases in PA, respectively. Details on these measures can be found in Table S3 in Multimedia Appendix 3.

#### Contextual Moderators

Contextual moderators will be collected at the in-person baseline data collection visit. The neighborhood environment will be assessed using a validated survey about neighborhood safety, crime, and areas to engage in PA [36]. Social determinants of health, including age, income, education level, marital status, and economic hardship will be assessed using validated questions that the principal investigator has used in prior studies. These have been chosen as they can impact PA levels [37,38]. The comorbid conditions of interest are obesity and depression as they are known to moderate PA levels and asthma outcomes [39,40]. Obesity is defined as a BMI ≥30 kg/m^2^, and depression will be assessed by a validated depression questionnaire, Patient Health Questionnaire Depression Scale-8 [41].

#### Implementation Measures

We propose an explanatory sequential mixed methods design in which quantitative analyses are followed by qualitative analyses to maximize our understanding of the implementation of ACTION [42,43]. The quantitative data will include detailed process metrics and surveys, and qualitative data will include brief interviews with participants. Process metrics will be collected based on the number of participants screened and randomized. Surveys to assess the acceptability of the intervention components will be collected at the end of each group session and at the end of the intervention (after group session 6). Evaluations of the intervention will be conducted using open-ended questions with intervention participants at 24- and 48-week data collection visits. Questions will focus on aspects of the intervention they found helpful, barriers to engagement in each component of the intervention (eg, groups, remote health coach, and Fitbit), and suggestions for improvement. General prompts will be used to orient qualitative data descriptively on the core intervention components. The qualitative portion of the intervention will be conducted by trained and experienced data collectors at the end of the brief quantitative data collection, audio-recorded, and professionally transcribed.

### Data Analysis Plan

Data will be analyzed based on the intent-to-treat principle in this multisite RCT. We will use descriptive statistics to describe the sample by intervention group, and any assumption behind each statistical method will be examined during the analysis. Missing data will be handled by each model’s assumption or by using multiple imputation with a fully conditional specification approach, as appropriate [44]. A 2-sided *P* value less than .05 would be considered statistically significant, and the exact *P* value will be reported. All quantitative analyses will be conducted by using SAS (version 9.4; SAS Institute Inc) and R (version 4.0.2; R Core Team).

The primary research outcome for aim 1A is the differences in ACQ score between baseline and 24 weeks for aim 1A and between baseline and 48 weeks for aim 1B. This will be compared between education control and ACTION intervention groups first using 2 sample *t* test to examine the efficacy and the maintenance effect of the proposed intervention, respectively. Two-tailed statistical tests will be conducted throughout the entire analysis unless specified otherwise. A linear mixed model with a subject-level random intercept then will be built on the same outcome in its original scale having time (12 weeks vs baseline; 24 weeks vs baseline; 48 weeks vs baseline), group (ACTION vs education control), and their interaction as the main factors while adjusting for site, recruitment wave, and any imbalanced confounder [45]. This model will allow us to estimate the efficacy of the intervention through the interaction terms after controlling for confounders and subject dependence. Moreover, any missing data can be handled by this model under the missing at random assumption. The estimated coefficients on the mean scale of the outcome will be reported, along with their SEs, 95% CIs, and *P* values. The similar modeling approach mentioned above using generalized linear mixed models instead will be applied to secondary outcomes (asthma quality of life, health care use, and asthma exacerbations) as secondary analyses.

For aim 2, we will explore the potential mediation effects of multiple variables on the relationship between the intervention and clinical outcomes. That is, a portion of the intervention effect on an outcome may be going through the path via a mediator indirectly. Through mediation analysis, the direct effect, the indirect effect also known as the mediated effect, and their total effect will be measured using the approach by Yu et al [46,47] along with their CIs via bootstrapping. The multiple mediators of interest here include social support, self-regulation, self-efficacy, and PA, while the clinical outcomes of interest are the ACQ score and mini-AQLQ score. To avoid the problem of mediation analysis with cross-sectional data, we define the mediation relationship generally noted as *X*-*M*-*Y*, using *X_BL_* as the exposure at baseline, *M_j_*_,24w_ as the *j*th mediator at 12 weeks (*j*=1,…, 6), and *Y*_k,48w_ as the *k*th outcome at 48 weeks (*k*=1,2) [48]. As a secondary analysis, multilevel mediation analysis using the method by Yu and Li [49] will also be considered. For moderation analysis, we will examine moderators including comorbid conditions (depression and obesity), social determinants of health (age, income, and education level), asthma severity (mild, moderate, and severe), and neighborhood environment (walkability and safety) by separately adding their interaction terms with the treatment group to the models mentioned for aim 1A to estimate their moderating effects on treatment responsiveness. We will focus on several plausible behavioral mechanisms. We anticipate improved PA will lead to improved asthma outcomes (control and quality of life) and a reduction in self-reported exacerbations and emergency health care use.

For aim 3, we will report process metrics, such as recruitment rate, monthly to assess reach overall, within key patient subgroups, and each site. Simple descriptive statistics and 95% CIs will be used to summarize measurement for reach and implementation potential at the end of the study. To identify participant characteristics (eg, age, income, and education level) or site-level factors that may be associated with reach, we will examine those associations using the chi-square test or Fisher exact test for categorical variables and the Kruskall-Wallis test for continuous variables. For analysis of qualitative data, the deidentified interview transcripts will be uploaded to the qualitative data software (eg, NVivo [OSR International] or Dedoose [University of California, Los Angeles]). Qualitative assistants will work with qualitative experts to code the data. All coders will initially read all 112 transcripts to become familiar with the data. Thematic interpretation will focus on individual, social, and structural factors associated with acceptability and reasons for variability in uptake and effectiveness of the intervention components. Ten transcripts will be independently coded by all coders. The codes will be reviewed and discussed collectively to develop a shared understanding of how the codes should be applied to the transcripts. This process of independent coding will be repeated ≥2 times until a consistent agreement is reached. Coded transcripts will be sorted to identify thematic groupings. The thematic groupings will be reviewed to identify emergent themes within each domain of the coding framework and quotes that best represent each domain.

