**Methods:**

The proposed study (ACTION [A Lifestyle Physical Activity Intervention for Minority Women with Asthma]) delivers a 24-week lifestyle walking intervention designed for and by urban Black women with asthma. Participants (n=224) will be recruited through 2 urban health care systems that care for a diverse Black population. Patients will be randomized to one of two groups: (1) ACTION intervention (group sessions, physical activity self-monitoring—Fitbit, and text-based support for step goal setting) or (2) education control (an individual asthma education session and SMS text messages related to asthma education). Outcome assessments will take place at baseline, 12, 24, and 48 weeks. The primary outcome is a change in asthma control from baseline to week 24 as assessed by the asthma control questionnaire-6 (ACQ-6). Secondary outcomes include asthma-related quality of life, health care use, and asthma exacerbations and behavioral outcomes such as self-efficacy, self-regulation, social support, and physical activity.

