### Study Design

This is a 2-arm RCT enrolling participants at the University of Chicago and the University of Illinois at Chicago in which 224 Black women with asthma will be randomly assigned to an education control group or receive ACTION intervention for 24 weeks (Figure 2). The remaining 24 weeks is the maintenance phase, and participants in the intervention group will receive 1 booster group session at ~36 weeks. Assessments will occur at 0, 12, 24, and 48 weeks.

The primary efficacy end point is a change from baseline to week 24 asthma control as assessed by asthma control questionnaire-6. We hypothesize that ACTION will be superior to education control for improving asthma control by week 24. The 48-week time point is important for examining behavioral mediators, contextual moderators, and maintenance of intervention effects.

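### Neither planned week-24 efficacy analysis conditions on baseline ACQ, and the two are not ranked; one baseline-adjusted primary analysis would be more precise

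*Protocol article*

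**What the plan says.** The Study Design section of the protocol article states: "The primary efficacy end point is a change from baseline to week 24 asthma control". The abstract gives the same single primary outcome.

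The Data Analysis Plan describes the primary research outcome as the difference in ACQ score "between baseline and 24 weeks for aim 1A and between baseline and 48 weeks for aim 1B". It gives two analyses of it. First: "This will be compared between education control and ACTION intervention groups first using 2 sample" (t test), with no covariates. Second: "A linear mixed model with a subject-level random intercept then will be built on the same outcome in its original scale". The fixed effects of that model are time (each of weeks 12, 24 and 48 against baseline), group and their interaction. It is adjusted for site, recruitment wave and any confounder found to be imbalanced.

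The t test is said to examine efficacy at 24 weeks and maintenance at 48 weeks. The mixed model is said to estimate efficacy through its interaction terms. The significance rule is one for all tests: a two-sided P "value less than .05 would be considered statistically significant". No sentence says which of the two analyses carries the week-24 conclusion.

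**The concern.** A mixed model that follows an unadjusted t test looks as if it supplies the baseline adjustment that the t test lacks. As specified, it does not. Baseline ACQ enters as a response at the first time level, and the group main effect lets the arms differ freely at baseline. The week-24 interaction is therefore again a difference in change from baseline.

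A change score subtracts baseline with a slope fixed at 1. When the regression of week-24 ACQ on baseline ACQ is shallower than that, as it is with equal variances and a correlation below 1, part of the baseline noise is carried into the treatment estimate. Randomisation keeps the estimate unbiased, but its variance is larger than it need be on the trial's one primary question.

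The second issue is that two analyses are offered for the same question without ranking. They agree closely with complete data but may part company when week-24 scores are missing or when the model's covariates move the estimate. The article gives no rule for that case.

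**Working it through.** **No stated figure to reproduce.** The article gives the sample size ("Participants (n=224) will be recruited through 2 urban health care systems") but no effect size, standard deviation, power, dropout rate or correlation behind it. The check therefore compares two analyses of the same data.

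**Step 1: is the model term a change-score contrast?** With every visit observed, a model with group, time and their interaction fits each group-by-visit mean. The week-24 interaction is then

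(mean at week 24 − mean at baseline) in ACTION − (mean at week 24 − mean at baseline) in control.

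Covariates that are constant within a woman, such as site, cancel from it. One simulated data set (224 women, 112 per arm, four visits, correlation 0.5, no missing values) confirms this. The allocation ratio is not stated; 112 per arm is an assumption suggested by "All coders will initially read all 112 transcripts to become familiar with the data", since the interviews are with intervention participants.

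- Mixed-model interaction at week 24: −0.18108 (SE 0.135)
- Difference in mean change: −0.18108 (SE 0.131)
- Week-24 score adjusted for baseline: −0.197 (SE 0.110)

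**Step 2: relative variance.** Let both visits have variance σ² and correlation ρ, and let k = 1/n₁ + 1/n₀.

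- Change score: 2(1 − ρ)σ²k
- Baseline-adjusted: (1 − ρ²)σ²k
- Ratio: (1 − ρ²) / [2(1 − ρ)] = (1 + ρ)/2

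The ratio does not depend on the allocation.

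**Step 3: what it is worth.** Take a comparison with 80% power on the change score at two-sided 0.05 (the 80% is an assumption). Its standardised effect is 1.9600 + 0.8416 = 2.8016. With adjustment, power is Φ(2.8016/√ratio − 1.9600).

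| Assumed ρ | Ratio (1+ρ)/2 | 224/ratio | 2.8016/√ratio | Power |
|---|---|---|---|---|
| 0.4 | 0.70 | 320 | 3.349 | 92% |
| 0.5 | 0.75 | 299 | 3.235 | 90% |
| 0.6 | 0.80 | 280 | 3.132 | 88% |
| 0.7 | 0.85 | 264 | 3.039 | 86% |

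The third column is the number of women who would be needed on change scores to match 224 analysed with adjustment. Over a wider range of ρ, 0.3 to 0.8, the ratio is 0.65 to 0.90 and power is 93.5% to 84.0%.

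**Step 4: does the lack of ranking inflate type I error?** In 20,000 simulated null trials with complete data, under each of two correlation structures, the t test rejected in 4.7% to 4.9%, the mixed model in 4.5% to 5.0%, and at least one of them in 4.9% to 5.4%. The effect on error is small.

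**The case against.** The strongest defence is that nothing here is invalid. The change-score comparison is unbiased under randomisation and holds its error rate. If 224 was derived for a change score, the planned power is intact and adjustment is a bonus. That stands: this is a point about precision, sized on an assumed correlation. A statistical analysis plan that is not shown may also name the decisive analysis. That stands too as far as ranking goes. It does not touch the form of the two analyses, which the article itself fixes, nor the fact that it assigns efficacy to both. The clause on imbalanced confounders does not help either, because baseline ACQ is already a response in the model.

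Several stronger readings are tempting, but the documents do not support them:

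- **Two primary time points with inflated error.** A reader might infer this from the sentence that lists 24 and 48 weeks together. But the abstract and Study Design fix week 24 alone, Objectives and Aims makes 48 weeks the separate maintenance aim 1B, and the Data Analysis Plan itself links the two weeks to efficacy and maintenance respectively. A familywise error of roughly 8% to 9% would arise only if a win at either week counted as efficacy, and no section says that. What is left is a sentence to reword.
- **A t test with no provision for missing data, at odds with intention to treat.** The Data Analysis Plan also allows multiple imputation by fully conditional specification where appropriate, which can serve the t test. The baseline section places randomisation after baseline data collection is complete.
- **Baseline ACQ thrown away.** A change score does use it, with a fixed slope. With equal variances and ρ above 0.5, it beats a comparison of week-24 scores alone.

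**Conclusion.** The point holds as one of precision and clarity. Both specified week-24 analyses rest on the change-score contrast, neither conditions on baseline ACQ, and the article does not rank them. The baseline-adjusted variance would be 0.70 to 0.85 of the change-score variance, which turns 80% power into about 86% to 92%.

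These figures assume equal ACQ variance at baseline and week 24, a correlation of 0.4 to 0.7, complete data and a starting power of 80%; the article gives none of these. If week-24 scores are more variable than baseline scores, the best slope (ρ times the ratio of week-24 to baseline standard deviation) moves towards 1 and the gain shrinks. In a trial of this size, adjustment would not be expected to do materially worse than the change score.

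The plan is not biased, and its week-24 test is not invalid. Having both a t test and a model adds little type I error with complete data. The practical risk is a disagreement between them under dropout, which the article's limitations section accepts may differ between arms.

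**What to change.** In the Data Analysis Plan:

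1. Name one primary analysis: the week-24 group difference in ACQ-6 from a repeated-measures model with weeks 12, 24 and 48 as responses and baseline ACQ, interacting with visit, as covariate. The equivalent alternative keeps baseline as a response but constrains the arms to a common baseline mean; this form retains every randomised woman with a baseline score.
2. Make the two-sample t test on change supportive.
3. Reword the sentence on the primary research outcome so that week 24 alone is primary, in line with the abstract and Study Design, and week 48 is the secondary maintenance outcome for aim 1B.

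The cost is wording. Baseline ACQ is already collected at the baseline visit, so no data, visits or participants are added. At submission 76 women had been recruited and completion was expected in 2027. The change should be recorded before outcomes are examined by arm, because a choice between the two analyses made after that would carry less weight.

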### Intervention

#### Overview

ACTION is a behavioral lifestyle intervention that promotes lifestyle PA in accordance with the current PA guidelines in the United States [17]. This intervention is a 24-week group lifestyle PA intervention consisting of 7 group sessions, PA self-monitoring, and text-based support for goal setting. The active period of the intervention is 24 weeks. Trained interventionists and remote health coaches deliver the intervention via a combination of in-person group walking sessions and text-based goal setting. Trained research staff provide a Fitbit for the participant and deliver the text messaging component of the intervention.

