##### Sessions 2-7

Women attend a 2-hour, in-person, or video remote group meeting at a convenient time during the induction or adoptive phases (weeks 0-24) and once during the maintenance phase (weeks 25-48). Participants from the individual sites are kept separate and do not attend group sessions together. Group session content is described in Textbox 2.

After 24 weeks of active intervention, participants randomized to ACTION no longer receive remote health coach text messages and attend monthly group sessions. A booster group session at 36 weeks will occur for the intervention group only.

Content of ACTION (A Lifestyle Physical Activity Intervention for Minority Women With Asthma) group sessions.

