**Sessions 2-7 (weeks 5,9,13, 17, 21, and 36)**
Video (10 minutes) on physical activity topics (eg, identifying realistic expectations for PA outcomes with asthma, handling personal and environmental problems that interfere with physical activity, and handling relapses)Group discussion and problem-solving (45 minutes)Group stretching and walking (20 minutes)

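### The planned primary tests allow for no correlation within ACTION session groups; if there is any, standard errors are too small and the type I error exceeds 5%

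*Protocol article*

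**What the plan says.** **Randomisation.** The unit is the woman: under Study Design, "224 Black women with asthma will be randomly assigned to an education control group or receive ACTION intervention for 24 weeks".

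**Delivery.** The Intervention Overview states "This intervention is a 24-week group lifestyle PA intervention consisting of 7 group sessions". Textbox 2 puts these at weeks 0, 5, 9, 13, 17, 21 and 36, so six fall before the 24-week endpoint. For sessions 2 to 7 it lists "Group discussion and problem-solving (45 minutes" among the contents, plus 20 minutes of stretching and walking as a group. Groups are formed within site: "Participants from the individual sites are kept separate and do not attend group sessions together".

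**Analysis.** The Data Analysis Plan first compares the ACQ change between arms by a two-sample t test, at 24 weeks for aim 1A and 48 weeks for aim 1B. Then "A linear mixed model with a subject-level random intercept then will be built on the same outcome", with time, group and their interaction, adjusted for site, recruitment wave and imbalanced confounders. The only dependence this model is said to control is that within a subject. Secondary outcomes get similar generalized linear mixed models.

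**Control arm.** The abstract and the Project Overview describe the control education session as individual. The Education Control Group section describes it as a group session.

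**The concern.** Women who discuss problems and walk together for months may come to have similar outcomes. The trial's own theory allows for this, since social support is a named mediator under aim 2. That makes the design partially nested: independent women in one arm, and women clustered within session groups in the other, with the clustering arising only after randomisation.

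The t test treats all women as independent. The mixed model links repeated measures on one woman but treats different women as independent. If changes are correlated within groups, both understate the variance of the ACTION mean. The estimated effect is not biased, but its confidence interval is too narrow and its P value too small. This bears on the primary efficacy claim at 24 weeks, on the maintenance claim at 48 weeks and, by the same reasoning, on the secondary outcomes.

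**Working it through.** **Inputs from the article**
- Two-sided 5% level: a *P* "value less than .05 would be considered statistically significant".
- 224 women in total. The allocation ratio is not stated; 112 per arm is inferred from 224/2 = 112 and from the qualitative plan, where "All coders will initially read all 112 transcripts to become familiar with the data".
- Neither an ICC, a group size nor a power calculation is given, so there is no stated figure to reproduce.

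**Assumptions:** stable ACTION groups of size m = 6 to 15 (112/15 ≈ 7 to 112/6 ≈ 19 groups), independent controls, complete data, and an ICC ρ of the change score from 0 to 0.10.

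**Formula.** With change-score variance σ² and 112 per arm:
- Variance assumed by the plan: 2σ²/112.
- Actual variance: (σ²/112)[1 + (m−1)ρ] + σ²/112.
- Ratio VR = 1 + (m−1)ρ/2. The correct SE is √VR times the reported one.
- Actual two-sided error = 2[1 − Φ(1.960/√VR)].

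**Worked cases**
- m = 6, ρ = 0.01: VR = 1 + 5 × 0.01/2 = 1.025; √VR = 1.012; error 5.3%.
- m = 10, ρ = 0.05: VR = 1 + 9 × 0.05/2 = 1.225; √VR = 1.107; error 7.7%.
- m = 15, ρ = 0.10: VR = 1 + 14 × 0.10/2 = 1.70; √VR = 1.304; error 13.3%.

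| m | ρ = 0 | 0.01 | 0.02 | 0.05 | 0.10 |
|---|---|---|---|---|---|
| 6 | 5.0% | 5.3% | 5.6% | 6.5% | 8.0% |
| 8 | 5.0% | 5.4% | 5.8% | 7.1% | 9.2% |
| 10 | 5.0% | 5.5% | 6.0% | 7.7% | 10.4% |
| 15 | 5.0% | 5.8% | 6.6% | 9.2% | 13.3% |

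**Simulation** (20,000 trials per setting, 112 per arm, no dropout):

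| m, ρ | t test | subject-intercept model | test on ACTION group means, Satterthwaite df |
|---|---|---|---|
| 8, 0 | 5.2% | 5.1% | 5.2% |
| 8, 0.02 | 6.0% | 6.0% | 5.1% |
| 8, 0.05 | 6.9% | 7.1% | 4.9% |
| 8, 0.10 | 9.2% | 9.6% | 5.1% |
| 14, 0.05 | 8.7% | 8.8% | 5.1% |

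The subject intercept gives no protection. Accounting for session group restores the nominal level.

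**Does adjusting for site and wave help?** No. Both are constant over time, so with complete data they cancel from the time-by-group contrast. In a simulated data set the 24-week interaction was −0.0243 (SE 0.1207) both with and without them.

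**If controls were grouped too**, with the same m and ρ, VR = 1 + (m−1)ρ. The case m = 10, ρ = 0.05 then gives VR = 1.45 and an error of 10.4%.

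**The case against.** **The inflation is not established.** A reader might infer that the type I error of this trial does exceed 5%. The article does not support that: it gives no ICC or group size, and at ICC 0 the planned tests hold their level. This objection stands, and the conclusion is conditional.

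**Groups may not be stable.** The article does not say that membership is fixed. Sessions 2-7 are scheduled for convenience, and the limitations section allows hybrid attendance. Mixing would weaken the nesting. This stands too.

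**Much of ACTION is individual.** Step goals are set with a coach by text, each woman has her own Fitbit, and the Figure 2 legend makes two group sessions remote. This argues against presuming the upper end of the ICC range, but it does not show that the correlation is zero.

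**One-arm clustering is not certain.** A reader might take controls to be independent. The article contradicts itself on this, so the table above holds only if their session is individual or leaves no correlation.

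**Direction.** A reader might say the error favours ACTION. Under the null the excess is symmetric: an error of 7.7% means about 3.8% false claims of benefit against a nominal 2.5%.

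**The article condenses a fuller plan.** True, but it does not leave the point open. It states the random-effects structure and the dependence that structure handles, and session group is in neither.

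**Conclusion.** The point holds in conditional form. The stated analyses are valid only if change scores are uncorrelated within session groups, and the article gives no reason to assume that of an intervention built partly on group discussion and walking. With any positive correlation, the SE is too small and the two-sided type I error is above 5%.

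Over the assumed range, with stable groups in the ACTION arm only, the error is about 5.3% to 13.3% and the correct SE about 1% to 30% larger than reported. Mixed groups would give less. The figures concern the continuous ACQ change with complete data. The same mechanism applies to health care use and exacerbations, but its size there was not computed.

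It would go too far to infer that 224 women are too few, since the article gives no power inputs to test that against.

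**What to change.** 1. Record for every ACTION woman the session group she is assigned to, or first scheduled into, after randomisation. Analyse by that group, not by sessions attended.
2. Make a partially nested mixed model the primary test in place of the unadjusted t test: the planned model plus a random session-group effect on post-baseline ACTION observations, with Satterthwaite or Kenward-Roger degrees of freedom. Use the analogous term for secondary outcomes.
3. Report the ICC, the number and sizes of groups, and how far women moved between them.
4. Reconcile the abstract and Project Overview with the Education Control Group section. If control education is individual, controls enter as singletons; if it is in groups, they need a group term as well.

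**Cost.** One stored identifier and one model term. At submission 76 of 224 women had been recruited, so the identifier could be recorded prospectively for most of the sample. Confidence intervals widen, degrees of freedom fall, and with few groups the group variance will be imprecisely estimated.

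Nominal power also falls. If 224 women gave 80% power without clustering (an assumption), power would be about 79% at m = 6, ρ = 0.01; 73% at m = 8, ρ = 0.05; 67% at m = 8, ρ = 0.10; and 57% at m = 15, ρ = 0.10. Keeping 80% would take about 224 × VR women: 230, 263, 302 and 381.
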